# ELEVATE – evaluating Temozolomide and Nivolumab in patients with advanced unresectable previously treated oesophagogastric adenocarcinoma with MGMT methylation: study protocol for a single arm phase II trial

**DOI:** 10.1186/s12885-022-09891-9

**Published:** 2022-09-01

**Keywords:** Oesophagogastric adenocarcinoma, Immunotherapy, MGMT methylated, Phase II

## Abstract

**Background:**

For patients with oesophagogastric adenocarcinoma, surgery is the only curative option and despite the use of multimodality therapy, which combines it with chemotherapy and/or radiotherapy, more than 50% of patients will relapse and die. Many UK patients present with advanced disease which is already inoperable or metastatic at diagnosis. For these patients, standard care chemotherapy only offers them survival of less than a year. Nivolumab, a checkpoint blockade inhibitor, has been found to work in some advanced cancers. It is proposed, for those where immunotherapy hasn’t worked, that these immunologically evasive tumours need to be sensitized to immunotherapy drugs to allow them to act.

**Methods:**

ELEVATE is a single arm phase II trial testing the overall response to nivolumab following temozolomide treatment in patients with advanced unresectable previously treated adenocarcinoma which is O^6^-methylguanine-DNA-methyltransferase (MGMT) methylated. 18 patients are being recruited from UK secondary care sites. To be eligible, participants must have been treated with at least 3 months of platinum and fluoropyrimidine chemotherapy. Participants will receive 50 mg/m^2^ temozolomide continuously for 3 months. If their disease progresses during the 3 months, they will stop temozolomide and start nivolumab at a dose of 240mg every 2 weeks. If there is no progression after 3 months the participant will continue taking temozolomide in combination with nivolumab. All treatment will stop once the participant progresses on nivolumab. The primary endpoint is the best overall response to nivolumab, using both Response Evaluation Criteria in Solid Tumours version 1.1 and immunotherapy modified Response Evaluation Criteria in Solid Tumours. Secondary endpoints include progression-free survival, overall survival, and quality of life.

**Discussion:**

ELEVATE will provide evidence for whether giving nivolumab after temozolomide in patients with previously treated advanced oesophagogastric adenocarcinoma is safe and biologically effective prior to future randomised trials.

**Trial registrations:**

EudraCT Number: 2020-004771-41(issued 01 October 2020); ISCRTN11398887(registered 14 July 2021).

**Supplementary Information:**

The online version contains supplementary material available at (10.1186/s12885-022-09891-9).

## Background

Gastric and oesophageal cancers are the 5th and 8th most commonly diagnosed cancers, respectively, and lead to more than 1.1 million deaths per year globally [1]. Although the incidence of distal gastric cancers has fallen sharply, the incidence of lower oesophageal and gastro-oesophageal junctional adenocarcinomas has risen rapidly in Western populations [2]. From 2014-2016 there were approximately 9,100 new oesophageal cancer cases in the UK every year and 7,900 oesophageal cancer deaths. In the same period, there were 6,700 new stomach cancer cases per year and around 4,500 stomach cancer deaths annually [3].

For patients with oesophagogastric adenocarcinoma (OGA), surgery offers the only chance of cure, however despite optimum multimodality therapy (surgery plus chemotherapy or chemoradiotherapy), more than 50% of patients relapse and die from metastatic disease [4–6]. Additionally, in the UK, most patients present with advanced, inoperable, or metastatic disease [3]. In advanced OGA (unresectable or metastatic cancer) treatment with the standard of care chemotherapy results in a median survival of less than one year in randomised trials, and although immunotherapy in combination with chemotherapy shows promise, the benefit of this approach appears to be limited to patients with high levels of PD-L1 expression [7–9]. Recommended standard of care chemotherapy in the first line setting usually includes a platinum and fluoropyrimidine, sometimes with the addition of a taxane or anthracycline; patients who have HER2 positive OGA are additionally offered trastuzumab [8–10]. In OGA, second line chemotherapy with a taxane or irinotecan results in an improvement in median overall survival of approximately six weeks in multiple international studies [11, 12]. The anti-VEGFR2 monoclonal antibody ramucirumab has monotherapy activity comparable to second line cytotoxic chemotherapy, and when added to paclitaxel, improves overall survival compared to paclitaxel alone, however ramucirumab is not funded in the UK for NHS patients [13, 14]. Therefore, novel approaches to improve survival for patients with advanced unresectable or metastatic OGA are desirable.

Immune checkpoint blockade therapy has revolutionised the treatment of multiple cancers including melanoma, lung, bladder and renal cancers [15–19]. Anti-PD-1 therapy has shown promise in the treatment of OGA patients. In the Asian ONO-4538-12 (ATTRACTION-2) trial, a phase III randomized study, 493 patients with chemo refractory unresectable advanced or recurrent oesophagogastric cancer were randomized 2:1 to either nivolumab 3mg/kg every two weeks or placebo [20]. Treatment with nivolumab improved median overall survival from 4.14 months to 5.32 months (HR 0.63; 95% CI (0.50-0.78), p<0.0001). Survival at 12 months was more than doubled for nivolumab treated patients (26.6% for nivolumab vs 10.9% for placebo). RECIST responses were observed in 12% of nivolumab patients, however tumour shrinkage was demonstrated in 40% of patients. A survival benefit for nivolumab treatment was observed for patients with and without PD-L1 expression (PD-L1 negative median OS 6.1 months vs. 4.2 months nivolumab vs placebo; PD-L1 positive median PS 5.2 months vs 3.8 months nivolumab vs. placebo). Thus, nivolumab is effective in chemo refractory gastric cancer independent of PD-L1 status. Similar results to those observed in Asian patients with single agent nivolumab in ATTRACTION-2 have been demonstrated in non-Asian patients in the CHECKMATE-032 study [21]. Pembrolizumab, a humanised immunoglobulin G4 monoclonal antibody targeting PD-1, has demonstrated similar results to nivolumab in OGA. In the non-randomised, international, KEYNOTE 059 study cohort 1,259 chemo refractory OGA patients (previously been treated with two or more lines of chemotherapy) were treated with pembrolizumab 200mg Q3W [22]. In KEYNOTE-059 cohort 1 RECIST responses were observed in 12% of all patients and 42% of patients had some evidence of tumour shrinkage, consistent with the results of nivolumab observed in the same setting [20, 21]. Following the results of ATTRACTION-2 and KEYNOTE-059 [22], nivolumab and pembrolizumab have been licensed in Asia and the USA for chemo refractory OGA (for PD-L1 positive patients only for pembrolizumab); however neither treatment is licensed in Europe for OGA patients.

Despite the early evidence of efficacy of anti-PD-1 therapy in chemo refractory OGA, immune checkpoint blockade inhibitors have not been successful in non-chemo refractory OGA disease settings in biomarker unselected populations. In the KEYNOTE 061 trial, pembrolizumab was compared to paclitaxel chemotherapy for second line OGA and failed to improve overall survival, either for PD-L1 positive (combine proportion score 1; primary endpoint) or PD-L1 negative cohorts [23]. However, a benefit of pembrolizumab compared to paclitaxel was observed for patients with microsatellite high tumours or who had tumour which expressed high levels of PD-L1 (Combined Proportion Score 10). In the first line KEYNOTE 062 trial, although pembrolizumab monotherapy was not inferior to chemotherapy in high PD-L1 (CPS 10 patients), in patients with low CPS scores neither pembrolizumab monotherapy, nor pembrolizumab plus chemotherapy were superior to chemotherapy alone [24]. Finally, in the CheckMate 649 trial, adding nivolumab to chemotherapy did extend overall survival, but only for patients with high PD-L1 expression (CPS 5) [9]. These findings emphasise that anti-PD-1 therapy is most effective in OGA patients who have been sensitised to immune checkpoint blockade therapy either through the presence of high mutation burden or other factors which lead to a robust immune infiltrate [25].

The enzyme O^6^-methylguanine-DNA-methyltransferase (MGMT) is responsible for removal of alkyl groups from the O^6^-position of guanine; when the MGMT promoter is methylated then protein expression is reduced and the capacity to repair O^6^-alkylguanine adducts is reduced, which can lead to increased sensitivity to alkylating agents. This is evidenced by modest radiological responses to single agent temozolomide (TMZ) or dacarbazine in MGMT methylated or protein negative tumours that do not characteristically respond when not biomarker selected (e.g. oesophageal or colorectal cancer (CRC) (9.4% ORR in oesophageal cancer) [26, 27]. Tumours which are MGMT methylated are sensitive to temozolomide.

Tumours which are MGMT deficient develop acquired mismatch repair deficiency as a resistance mechanism to TMZ treatment. In recent work, colorectal cell lines sensitive to TMZ (predominantly MGMT deficient) were treated with TMZ until resistance emerged and underwent molecular profiling. This revealed the frequent emergence of mismatch repair deficiency and a hypermutated state [28]. The same group went on to demonstrate that in a subset of CRC patients treated on clinical trials who initially benefited from TMZ and subsequently progressed, changes in mismatch repair (MMR) status were observed in the post-treatment biopsy in 40% of cases. The ELEVATE trial is the first to address this question in oesophagogastric adenocarcinoma patients.

TMZ is given on an intermittent or continuous basis, according to the indication, and regimens may have differential effects in evoking MMRd and on the immune microenvironment. For example, continuous dosing with TMZ can lead to T-reg depletion whereas standard dosing does not. T-reg depletion would be more favourable for a response to immune checkpoint blockade. Different TMZ dosing regimens also have different effects on lymphocytes, with consequent differences in antigen specific immune responses and outcomes both in the clinic and in animal models [29–35]. As continuous dosing is more likely to be better tolerated after first line chemotherapy due to low daily doses, this approach is favoured for the ELEVATE trial. TMZ will be dosed until progression, as the only practical clinical indication of TMZ resistance, required for the development of MMRd in experimental models [28].

## Methods/Design

The ELEVATE trial is a phase II trial evaluating whether Temozolomide and Nivolumab in patients with advanced unresectable previously treated oesophagogastric adenocarcinoma with MGMT methylation is safe and is biologically active.

## Objectives

The primary objective is to determine the activity of maintenance TMZ dosing followed by nivolumab treatment to evaluate the potential for a future randomised trial against a standard of care control arm. The rationale to continue TMZ for 3 months or until PD is to evaluate the emergence of Mismatch Repair Deficiency (MMRd) both with and without radiological PD, as clinically relevant MMRd may emerge before radiological progression. This will also reduce the number of patients who drop out due to symptomatic progressive disease.

Secondary objectives include determining the safety of TMZ and nivolumab, the effect of TMZ priming followed by nivolumab on disease control rates, progression free survival (according to RECIST v1.1 and iRECIST criteria), overall survival and safety and toxicity. The quality of life of trial participants will also be assessed using EORT-QLQ-C30, EORT-QLQ-OG25 and EQ-5D-5L questionnaires.

Exploratory objectives include identifying the proportion of patients treated with TMZ that develop MMRd, by comparing pre-TMZ and post-TMZ tumour biopsies. Understanding the relationship between MGMT protein expression, MGMT methylation and acquisition of MMRd, and the rate of increased acquisition of tumour mutation burden after TMZ and the relationship between Tumour Mutational Burden (TMB) acquisition and response to nivolumab will be explored. MGMT immunohistochemistry status after chemotherapy but before TMZ will be characterised. Another objective is to interrogate the response of the tumour microenvironment to immune checkpoint blockade. Tumour evolution of non-MMR genes will also be assessed under chemotherapy using archival, post-chemotherapy and post TMZ biopsies. ctDNA for tumour burden and clonal dynamics will be assessed comparing a baseline sample to post-TMZ and post nivolumab in relation to clinical and radiological response. We will correlate TMB in blood with TMB using Whole Genome Sequencing (WGS).

## Study design

ELEVATE is a multicentre single arm Phase II trial in patients with advanced unresectable previously treated oesophagogastric adenocarcinoma with MGMT methylation (Fig. 1), using an A’Hern’s single stage design [36].

**Fig. 1 Fig1:**
[figure not shown]
ELEVATE Trial schema

### Treatment

All participants will receive metronomic TMZ followed by nivolumab combination or monotherapy. Participants will receive TMZ 50 mg/m^2^/day for 3 months or until disease progression, determined by RECIST 1.1 criteria. TMZ dose will be rounded to the nearest 5 mg. TMZ is taken orally every day throughout the 28 day cycle. Capsules should be swallowed whole with a glass of water, at least one hour before or 2 hours after food. Missed doses of more than 12 hours late should not be taken. Participants treated with TMZ should receive 960 mg co-trimoxazole three times per week as prophylaxis against opportunistic infections. Anti-emetics can be given as per local practice. Participants should maintain a normal diet unless modifications are required to manage an AE such as diarrhoea, nausea or vomiting.

After 3 months of TMZ or following progression on TMZ (or other withdrawal from TMZ due to, for example, toxicity), whichever comes first, all participants will then receive nivolumab at 240 mg as a 30 minute infusion every 2 weeks +/- TMZ (where TMZ will only continue if the participant has not progressed or withdrawn from TMZ treatment). Treatment with nivolumab will commence within 3 weeks of TMZ progression or month 3 of TMZ treatment. Nivolumab +/- TMZ will continue until definitive disease progression (determined by iRECIST), a maximum of 24 months, death, or withdrawal from treatment or study. The Schedule of Events (Table 1) details the trial treatment schedule.

**Table 1 Tab1:** Schedule of observations and procedures (SPIRIT figure for ELEVATE – Additional file 4)

Visit:	Pre-Screen	Screening (within 28 days of C1)	Baseline (D1 C1 TMZ – 28 day cycle)	Day 1 of each TMZ cycle	Progression or cessation of TMZ or at month 3/day 84 (+/- 7 days)	Day 1 of each Nivo (+/- TMZ) cycle	Progression/End of treatment
Informed consent - Tumour analysis for MGMT methylation	X						
Archival tumour tissue to central laboratory	X						
Informed Consent		X					
Eligibility Evaluation		X					
Medical History		X					
Mismatch repair proficient testing (MSI-normal or MMR intact)		X					
Physical Exam^a^		X	X	X	X	X	X
Vital signs^b^		X	X	X	X	X	X
ECOG performance Status		X	X	X	X	X	X
Phone call to check compliance				X		X	
Echo/MUGA^c^		X					
Pregnancy test in WOCBP		X	X	X		X	
CT Scan^d^		X		X^e^	X^f^	X^g^	
Serum Chemistry (U&E^h^, LFTS^i^,CalciumCA19-9)		X	X	X	X	X	X
Endocrine tests: Morning cortisol, ACTH, TSH (Free T3 and Free T4 in case of abnormal TSH)		X				X^j^	
Full blood count		X	X^k^	X^k^	X	X^k^	
Serology – HBV or HCV		X					
ECG^l^		X					
Adverse Events		X	X	X	X	X	X
Concomitant Medication		X^m^	X	X	X	X	X
Patient registered with NHS Digital			X				
Quality of Life Questionnaires^n^			X	X	X	X	X
Details of next treatment							X
TRANSLATIONAL SAMPLES							
Tumour Biopsy (endoscopy)					X		X^o^
Translational blood (ctDNA, Plasma)		X	X	X^p^	X	X^q^	X

^a^Height and weight. Height only required at screening

^b^Temperature, blood pressure, heart rate, respiratory rate, oxygen saturation

^c^If clinically indicated

^d^Assessments performed following RECIST 1.1/iRECIST guidelines as appropriate)

^e^CT scans are required at week 6 and week 12 of TMZ treatment. Assessment of scan should be completed following RECIST 1.1 guidelines

^f^CT scan not required if cessation of TMZ occurs within 4 weeks of the week 6 scan

^g^CT scan at week 6 and week 12 of Nivolumab treatment and then every 12 weeks thereafter until CT scan demonstrates unconfirmed progression, following iRECIST guidelines, then a confirmatory CT scan should be performed 4-6 weeks later

^h^Urea and electrolytes

^i^AST and/or ALT, ALP, bilirubin

^j^Every 6 weeks on nivolumab (TSH, cortisol)

^k^FBC weekly whilst on TMZ

^l^Within 7 days prior to treatment start date

^m^To include all those being taken from 30 days prior to starting trial treatment and during treatment and up to 100 days after last study dose

^n^EORTC QLQ-C30, EQ-5D-5L & QLQ-OG25

^o^Optional endoscopy

^p^At 4-6 weeks from D1 C1 TMZ

^q^At 4-6 weeks from D1 C1 Nivolumab

There will be no dose escalations or reductions of nivolumab allowed. Participants may be dosed no less than 12 days from the previous dose. The infusion will be administered through a sterile, non-pyrogenic, low protein binding in-line filter with a pore size of 0.2-1.2 *μ*m. It will not be administered as an intravenous push or bolus injection. The total dose may be infused directly as a 10 mg/mL solution or can be diluted to as low as 1 mg/mL with sodium chloride 9 mg/mL (0.9%) solution for injection or glucose 50 mg/mL (5%) glucose solution for injection. The infusion will be administered over 30 minutes. After administration the line will be flushed with sodium chloride 9 mg/mL (0.9%) solution for injection or 50 mg/mL (5%) glucose solution for injection.

During continuous dose TMZ, the participants’ FBC should be checked weekly. TMZ can continue, providing the following conditions are met: 
Absolute Neutrophil Count (ANC) 1.5 x 10^9^/lThrombocyte count 100 x 10^9^/lCommon toxicity criteria (CTC) non-haematological toxicity Grade 1 (except for alopecia, nausea and vomiting).

Table 2 details the criteria for modifying the continuous dosing of temozolomide.

**Table 2 Tab2:** Dose modifications for continuous dosing temozolomide

Toxicity	Withhold TMZ (until counts return to above criteria)	TMZ discontinuation
ANC	0.5 and < 1.5 x 10^9^/l	< 0.5 x 10^9^/l
Platelets	10 and < 100 x 10^9^/l	< 10 x 10^9^/l
CTCAE toxicity (version 5)	Grade 2	Grade 3-4

While dose modifications are not permitted on this trial, there are a set of criteria that should be assessed when considering delaying, discontinuing or restarting nivolumab treatment in relation to adverse events and infusion related events (Additional file 1 explains these criteria in more detail).

Participants on IV steroids may be switched to an equivalent dose of oral corticosteroid (e.g. prednisolone) at start of tapering or earlier, once sustained clinical improvement is observed. Lower bioavailability of oral corticosteroids should be considered when switching to the equivalent dose of oral corticosteroids.

Prophylactic antibiotics should be considered in the setting of ongoing immunosuppression.

### Setting

ELEVATE will be run in 6-8 secondary care hospitals in the UK with the aim of recruiting up to a total of 18 evaluable patients.

### Sample size and recruitment

The sample size calculation was performed using Sample Size Tables for Clinical Studies. This phase II trial will be based on A’Hern’s single stage design [36]. The primary endpoint of objective response measured in ELEVATE is to nivolumab (following progression, or 3 months without progression, on TMZ), not to TMZ monotherapy, i.e., the baseline measurement for indicating response/progression is taken from the point of initiation of nivolumab.

Based on 10% alpha and 80% power, and assuming a response rate of <10% would not be sufficient activity to warrant further investigation in a future phase III, and a >30% response rate would warrant further investigation in a future phase II, the required sample size is 18. If 4 or more responses are observed in 18 patients then the treatment will be considered sufficiently active to justify its inclusion in a future phase III. The lower limit of 10% ORR was chosen based on this being expected when using nivolumab in unselected populations.

In order to identify 18 MGMT low/methylated patients and based on an estimated minimum 20% showing MGMT loss then, 90 patients will be required to be screened. We anticipate needing to screen approximately 120 patients to account for screen failures and a very small number of deaths in recruited participants prior to starting nivolumab.

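### The transition-CT waiver in Table 1 is counted to the end of temozolomide, not to the first nivolumab dose, so some primary-endpoint baseline scans can be more than 28 days old

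*Protocol article*

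**What the plan says.** All places are in the protocol article.

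- **Baseline.** Sample size and recruitment defines the endpoint as response to nivolumab, not to temozolomide alone, and adds that "the baseline measurement for indicating response/progression is taken from the point of initiation of nivolumab".
- **Routes into nivolumab.** Under Treatment, participants move on after progression, after 3 months, "or other withdrawal from TMZ due to, for example, toxicity), whichever comes first, all participants will then receive nivolumab". Table 2 makes stopping temozolomide mandatory for Grade 3-4 toxicity, very low neutrophils or very low platelets, so the withdrawal route is part of the plan.
- **Scans on temozolomide.** Table 1, footnote e: "CT scans are required at week 6 and week 12 of TMZ treatment".
- **Transition scan.** Table 1 lists a CT at the visit headed "Progression or cessation of TMZ or at month 3/day 84 (+/- 7 days", but footnote f says "CT scan not required if cessation of TMZ occurs within 4 weeks of the week 6 scan".
- **Scans on nivolumab.** Footnote g: "CT scan at week 6 and week 12 of Nivolumab treatment and then every 12 weeks thereafter". None is listed for day 1.
- **Start of nivolumab.** The three-week limit under Treatment names progression and month 3. It does not name withdrawal for other reasons.
- **Pre-temozolomide baseline.** The Table 1 column reads "Screening (within 28 days of C1", and the Screening section places the CT in that 28-day window.
- **Analysis set.** Statistical analysis includes everyone who received at least one dose of nivolumab.

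**The concern.** Footnote f measures the wrong interval. What matters for a nivolumab baseline is the time from the last scan to the first nivolumab dose. The footnote limits only the time from the scan to the end of temozolomide, and leaves out the gap that follows.

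A site that follows the schedule exactly may therefore have no scan after temozolomide week 6 for someone who stops for toxicity some weeks later. Any change in tumour size between that scan and the first nivolumab dose is then counted as change on nivolumab. Shrinkage in that interval makes a response easier to reach, and growth makes it harder.

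These participants are in the primary analysis. The secondary analysis, limited to those with at least two weeks of temozolomide, does not remove them. The decision is a count of 4 in 18, so one misclassified participant can reverse it, and no analysis plan can recover a scan that was not taken.

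**Working it through.** **1. The plan's own figure.** Inputs from Sample size and recruitment: n = 18, at least 4 responses, uninteresting rate 10%, interesting rate 30%, alpha 10%, power 80%. Exact binomial:

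- P(X ≥ 4 | n = 18, p = 0.10) = 0.0982
- P(X ≥ 4 | n = 18, p = 0.30) = 0.8354

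18 is the smallest n that meets both limits. The design reproduces and is not in question.

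**2. Age of the baseline scan.** Take the week 6 scan as day 42. Footnote f then waives the transition CT for stops up to day 70 (42 + 28).

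Scan age at first nivolumab dose = (stop day − 42) + gap from stop to nivolumab.

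| Temozolomide stops | Gap 0 d | Gap 7 d | Gap 14 d | Gap 21 d |
|---|---|---|---|---|
| Day 42 | 0 | 7 | 14 | 21 |
| Day 49 | 7 | 14 | 21 | 28 |
| Day 56 | 14 | 21 | 28 | 35 |
| Day 63 | 21 | 28 | 35 | 42 |
| Day 70 | 28 | 35 | 42 | 49 |

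The gaps are assumed values, because the article sets no limit for this route. The age is above 28 days in 6 of the 20 cells. All six need a stop at day 56 or later and a gap of at least 7 days.

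**3. The month 3 route for comparison.** Taking month 3 as day 84, nivolumab starts by day 84 + 21 = 105. A week 12 scan on day 84 is then 21 days old. With the 7-day visit tolerance (day 77) it is 28 days old. The route with a stated start limit therefore never exceeds 28 days, while the withdrawal route can.

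**4. What a change before nivolumab does to the response threshold.** Assume partial response means a 30% fall in the sum of diameters from baseline. If the sum changes by a fraction c between the old scan and nivolumab start, the fall needed on nivolumab is 1 − 0.70/(1 + c).

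| c | −20% | −10% | −5% | +5% | +10% | +20% |
|---|---|---|---|---|---|---|
| Fall needed | 12.5% | 22.2% | 26.3% | 33.3% | 36.4% | 41.7% |

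**5. Illustration on the decision rule.** Suppose one participant of 18 is affected, with response probability q in place of p. P(go) = P(Bin(17, p) + Bin(1, q) ≥ 4).

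- p = 0.10: q = 0.15 gives 0.1060 and q = 0.20 gives 0.1138, against 0.0982.
- p = 0.30: q = 0.25 gives 0.8292 and q = 0.20 gives 0.8230, against 0.8354.

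Both the values of q and the count of one affected participant are assumptions. The documents give neither.

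**The case against.** The case for leaving the footnote alone has several parts.

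- **The group is narrow.** A participant must stop without progression in weeks 6 to 10, still go on to nivolumab, and wait long enough to pass 28 days. Those who progress on the week 6 scan or reach the week 12 scan are not touched by the waiver. The article favours continuous low-dose temozolomide because it expects better tolerance. This stands, and it keeps the point small.
- **The waiver is permissive.** Sites may still scan, and the waiver spares a repeat CT soon after the last one. That is reasonable for a recent scan. But if sites choose, the baseline differs by site, and the footnote does not ask how recent the scan is when nivolumab starts.
- **Other text may cover it.** Footnote d says "Assessments performed following RECIST 1.1/iRECIST guidelines as appropriate", the full protocol is not shown, and the three-week sentence may be shorthand for all routes. Even so, footnote f is an explicit rule that says no scan is needed. If the three-week limit did apply, the table still reaches 49 days.
- **The 28-day limit is borrowed.** The article does not set it for the nivolumab baseline. It is the trial's own limit for the earlier baseline and matches the longest age on the month 3 route, so it is a reasonable standard but not a stated one.

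A reader might go further and infer that any scan taken during temozolomide is an invalid baseline, or that the waiver credits temozolomide responses to nivolumab. The documents do not support either. Participants without progression at month 3 continue temozolomide alongside nivolumab, so its later effect on the tumour is already within the endpoint by design. In 14 of the 20 cells above, the week 6 scan is no more than 28 days old. The direction of any bias is unknown.

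**Conclusion.** The point holds as a fault of scan timing. Followed exactly, footnote f lets a participant who stops temozolomide without progression in weeks 6 to 10 enter nivolumab with no scan after temozolomide week 6, and that baseline can be more than 28 days old. This conflicts with a baseline placed at the start of nivolumab, and it is looser than the 28-day limit used before temozolomide.

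The size is modest. The number affected is not given and is probably small. With one affected participant, under the assumed rates, the false-go probability moves from 9.8% to 10.6% or 11.4%, and power from 83.5% to 82.9% or 82.3%, still above 80%. These figures are illustrations and not estimates. The 35 to 49 day ages after a day 70 stop rest on assumed gaps of 7 to 21 days. The sample size, the analysis set and the 4-of-18 rule stand. It is worth correcting because the remedy is cheap and the missing scan cannot be recovered later.

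**What to change.** Reword footnote f of Table 1: *Transition CT not required if the last CT is within 28 days before the first nivolumab dose; otherwise repeat before dosing.*

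This limits the age of the baseline scan. It does not remove all temozolomide exposure after that scan: a stop at day 70 with nivolumab the same day would still use a scan followed by 28 days of temozolomide. One side effect is that a participant who stops very early could have a recent pre-temozolomide scan accepted. If that is not wanted, restrict the waiver to scans taken on temozolomide.

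The cost is one footnote, and one CT for each participant whose last scan is older than 28 days. That CT is already listed at the transition visit. Nobody whose last scan is within 28 days of the first dose needs another.

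I would not add a fixed three-week start limit for those who withdraw for toxicity. It could press sites to dose before Grade 3-4 toxicity has resolved, and the reworded footnote controls scan age without it.
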